### Time of messaging

The messages will be sent to the intervention group only in the first 6 months from the baseline. The following time points measure the intervention’s long-term effect on biological markers, and the stages of change for healthy eating and physical activity.

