### Data analysis plan

Data will be analyzed using the Statistical Package for Social Studies (SPSS 22; IBM Corp., New York, NY, USA). Continuous variables will be expressed as mean ± standard deviation or median and interquartile ranges according to the normality assessment. Categorical variables will be expressed as frequencies and percentages.

The chi-square statistical test will be applied for categorical variables to assess the association between them. The t-test or Mann-Whitney test will be used to compare numeric variables. Repeated measures analysis of variances or Friedman’s test will be used to evaluate repeated measures over the follow-up period.

The incidence rate and cumulative incidence rate will be computed for incidence of T2DM among the intervention and control groups. Additionally, comparison between the incidence of T2DM among different age groups and gender will be evaluated. Kaplan-Meier survival curves and log-rank tests will be used to compare the intervention and control groups as well as the different risk groups for progression to T2DM, and transition and/or relapses from different stages of TTM.

Hazards ratios with 95% confidence intervals will be calculated and the adjustment of known confounders will be adopted in the Cox regression model. In all the analyses, *P*-values < 0.05 will be considered statistically significant.

The principal analyses of primary and secondary outcomes will use the intent-to-treat approach. The intent-to-treat analyses will include all participants in their randomly assigned treatment groups regardless of a participant’s adherence to the assigned treatment regimen.

All data entry will be anonymous and identification numbers will be saved in a password-protected log file with the primary investigator. Backup of entered data will be created monthly to avoid any loss of collected data. An interim analysis of data will be conducted 12 months after recruitment of the last participants. Interim analysis aims to evaluate the completeness and accuracy of the collected data and early detection of any difficulties.

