### Sample size calculation

A sample size of 300 is required so that there are 150 participants each in the intervention and control groups. The sample size was calculated by using Stata® software version 15 (StataCorp, College Station, Texas, USA) with the assumptions that α = level of significance (0.05), β = Type II error (power of the study = 1- β = 80%). The hazard rate of diabetes development among the control group is 10% over the 2 years, the hazard rate of diabetes development among the intervention group is 7% over the 2 years (reduction of about 30%) and the minimum sample size required to reject the null hypothesis is 256 (128 in each group). With an expected loss of follow-up around 20%, the sample size was increased to 300 participants in total.

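### The assumed 7% two-year risk rests on an unstated carry-over effect after messaging stops at month 6, and the stated 80% power is sensitive to it

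*Protocol article*

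**What the plan says.** The Sample size calculation of the Protocol article takes "α = level of significance (0.05"), "power of the study = 1- β = 80"%, and these rates: "The hazard rate of diabetes development among the control group is 10% over the 2 years" and "the hazard rate of diabetes development among the intervention group is 7% over the 2 years (reduction of about 30"%). It concludes that "the minimum sample size required to reject the null hypothesis is 256 (128 in each group"), raised to 300 for about 20% loss. It gives no source for the 30% and does not say how the effect is spread over the 2 years.

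Under Time of messaging: "The messages will be sent to the intervention group only in the first 6 months from the baseline". The same section adds: "The following time points measure the intervention’s long-term effect on biological markers", together with the stages of change for diet and activity.

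Under Lifestyle education, both arms get the same baseline education and background treatment, only the intervention arm gets messages, and neither arm gets further lifestyle advice in person unless a participant asks.

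The Data analysis plan states: "Kaplan-Meier survival curves and log-rank tests will be used to compare the intervention and control groups". It adds Cox hazard ratios, incidence rates and cumulative incidence by arm, analysed by intention to treat. It names no period-specific estimate.

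**The concern.** The sizing horizon is four times as long as the intervention. From month 6 onward the protocol plans no difference between the arms, yet the reduction of about 30% is an average over all 24 months. Whether an effect outlasts the messages is something the later visits are meant to measure, and the sample size depends on the answer without saying so.

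If the effect wanes, the overall hazard ratio moves toward 1 and longer follow-up can weaken the log-rank test. A null result could then be read as showing that the messages do not work, when they may have worked while they were sent.

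**Working it through.** **Reproducing the plan's figure.** The 256 comes from the exponential-hazard comparison with hazards 0.10 and 0.07, two-sided 0.05, 80% power and no censoring:

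[(1.96·√(4·0.085²) + 0.8416·√(2·0.10² + 2·0.07²)) / 0.03]² = 254.4, so 128 per arm.

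This treats every participant as followed to diabetes, so 256 is in effect a number of events (Schoenfeld gives 247 at a ratio of 0.70). That is a separate problem. It matters here because it already lowers the power before waning is considered.

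**Inputs.** Control risk 10% and intervention risk 7% at 2 years (Sample size calculation); messaging for 0.5 year (Time of messaging). The constant control hazard is my assumption.

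- Control hazard: h = −ln(0.90)/2 = 0.0527 per year.
- Intervention hazard if constant: −ln(0.93)/2 = 0.0363 per year; ratio 0.689.

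**Ceiling for an effect confined to messaging.** Zero hazard for 6 months, then the control hazard:

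1 − exp(−1.5·0.0527) = 1 − 0.9^0.75 = 7.6%.

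The average hazard ratio is 1.5/2 = 0.75. Reaching 7% by complete prevention alone takes 24·(1 − ln 0.93/ln 0.90) = 7.5 months. If the 10% is read as a cumulative hazard, the ceiling is 0.10·0.75 = 0.075 against 0.07, so the conclusion is the same.

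**Later hazard ratio needed for 7%.** With ratio r during messaging:

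later ratio = (0.0726 − 0.5·0.0527·r) / (1.5·0.0527), where 0.0726 = −ln 0.93.

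| Ratio in months 0–6 | Ratio needed in months 6–24 |
|---|---|
| 0 | 0.92 |
| 0.50 | 0.75 |
| 0.69–0.70 | 0.69 |

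**Two-year risk and participants needed.** The last column is the usual two-proportion size against 10% (two-sided 0.05, 80% power, no loss), so it is free of the events problem above.

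| Pattern | 2-year risk | Per arm |
|---|---|---|
| As assumed | 7.0% | 1,356 |
| Complete prevention, messaging only | 7.6% | 2,182 |
| Ratio 0.50, messaging only | 8.8% | 9,393 |
| Ratio 0.70, messaging only | 9.3% | 26,829 |

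For a ratio of 0.689 to month 6 that fades linearly to 1 at month 24, the average ratio is (6·0.689 + 18·0.845)/24 = 0.81 and the 2-year risk is 1 − 0.9^0.81 = 8.1%.

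**Power of the planned test.** Two-sided log-rank, 20,000 simulations per pattern, starting ratio 0.689, detection at 6-monthly visits, exponential loss of 20% per 2 years, 36 months of follow-up:

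| Pattern | 300 participants | 1016 participants |
|---|---|---|
| Constant | about 18% | about 48% |
| Fading by month 24 | 7% | 13% |
| Messaging only | 5–6% | 7% |

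The 1016 is the number that the Abstract says will be recruited. As a check on the first cell, a constant effect in 300 people gives about 31 events, and Φ(0.5·√31·0.3725 − 1.96) = Φ(−0.92) = 18%.

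With zero hazard during messaging and the control hazard afterwards, power for 1016 participants falls from 30% at 24 months to 22% at 36 months.

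**The case against.** The strongest answer is that the protocol expects change to last. The intervention aims to move people to the maintenance stage, defined in Table 1 as change held for more than 6 months, and later visits are planned to follow long-term effects. The sizing needs an average reduction of about 30%, not a constant one. A ratio of 0.50 during messaging and 0.75 afterwards loses half the effect and still gives 1 − exp(−0.0527·(0.25 + 1.125)) = 6.99%. Its power (16–17% for 300, 44% for 1016) is close to that of a constant effect. The Background cites a 50% reduction for lifestyle programmes, so 30% is not extravagant. All of this stands.

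It rules out two readings that a reader might infer: that 7% is out of reach or contradicts the messaging schedule, and that it requires undiminished carry-over. Both would need assumptions that the protocol does not make. Nor is assuming an effect under test an error in itself; every superiority calculation does so. What remains is that part of the assumed effect must occur after the intervention ends, and the text neither says how much nor gives a basis.

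A reader might also infer that the analysis cannot see waning. That goes too far: Kaplan-Meier curves, cumulative incidence by arm, repeated measures and stage relapse are all planned. It is the single overall hazard ratio and log-rank test that cannot separate the two periods. Finer modelling may sit in an analysis plan that is not shown, but the sizing assumption is fixed in the protocol.

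Finally, at 300 participants the events problem dominates the loss of power. That is true, but the per-arm sizes above show that correcting it on a constant 30% would still leave the trial too small if the effect wanes.

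**Conclusion.** The point holds as a gap in the sizing, not as a contradiction. With a constant control hazard, an effect limited to the 6 messaging months leaves at least 7.6% at 2 years, so 7% depends on an unstated later hazard ratio between about 0.92 and 0.69, according to the strength of the early effect. The ceiling would fail only if at least 31% of the 2-year control hazard (1 − 0.0726/0.1054) fell in the first 6 months; an even spread puts 25% there.

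The stated 80% power is not delivered at 300 participants under any pattern tested: about 18% constant, 7% fading, 5–6% messaging only. The fade patterns, the starting ratio of 0.689 in these three, and the timing of loss are assumptions; the document gives no persistence figure. The low starting point of 18% belongs to the events problem, and the drop from 18% to 5–7% belongs to this one.

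**What to change.** In the Sample size calculation, state the persistence assumed after month 6 and its basis, and replace the 80% figure with power under constant, fading-by-month-24 and messaging-only effects.

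In the Data analysis plan, keep the intention-to-treat log-rank test as the main test. Add as supportive analyses:

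- the arm difference in cumulative incidence, with 95% confidence interval, at months 6, 24 and 36;
- Cox hazard ratios by arm and period, with period 1 up to and including the month-6 visit (where events arising during messaging are detected) and period 2 after it.

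Judge persistence from the incidence differences together with both ratios. Do not rest it on the period-2 ratio alone: that compares only people still diabetes-free at month 6, a group formed after randomisation, and it can be near 1 while an incidence difference remains.

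The cost is a few sentences and one added model on data already collected. The downside is a less favourable stated power and wide period-specific intervals: with 300 participants, only about 6 events are expected by month 6.

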## Methods/design

### Study design (setting, eligibility and recruitment)

This is a three-year randomized controlled trial that includes Saudis ≥18 years of age. Participants for the present study will be recruited from the Heart Health Promotion study (HHP), which was conducted at King Saud University from 8 July, 2013 to 30 April, 2014 [20]. In the HHP study, participants were recruited from the three primary health care clinics serving the employees and their families at King Khalid University Hospital [20]. The HHP study was conducted on a large group of Saudi adults, who were at a higher risk of developing T2DM within 2–3 years. Recent data record updates of the original study on May 2017, revealed that out of the total sample (1234 prediabetic subjects) enrolled in the HHP study, 218 individuals had developed overt diabetes during the last 4 years (May 2013–May 2017). Therefore, 1016 are eligible for the present study.

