### Baseline visit

#### Lifestyle education

Eligible prediabetic subjects from the previous HHP study [20] will be invited to the HHP office. If they give consent for this trial, then participants will be assigned to either the intervention or the control group by the computer-generated list. At this baseline visit, all participants will receive group education and motivation about lifestyle modifications along with written information about diet and physical activity recommendations offered by a diabetic educator and a physician. This will advise participants on balancing food intake and physical activity to achieve and maintain appropriate body weight. All participants will take Metformin 500 mg twice daily. In addition, only participants in the intervention group will receive SMS messages at frequent intervals. These messages will be about a healthy lifestyle, the benefits of physical activity and a healthy diet. Neither group will receive any additional lifestyle information or advice by personal contact after the baseline visit, except in response to specific queries from the participants.

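### The stated 256 participants (300 with loss) do not give 80% power for T2DM incidence: on the plan's own rates, 300 give about 15% at 2 years and 21% at 3 years

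*Protocol article*

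**What the plan says.** The Sample size calculation assumes alpha 0.05 and 80% power. Its rates are: "The hazard rate of diabetes development among the control group is 10% over the 2 years" and "the hazard rate of diabetes development among the intervention group is 7% over the 2 years", described as a reduction of about 30%. It concludes that "the minimum sample size required to reject the null hypothesis is 256 (128 in each group", and increases this to 300 in total for an expected loss of around 20%.

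Elsewhere in the protocol article:
- Study design: "This is a three-year randomized controlled trial". The Abstract lists assessments up to 36 months.
- The Abstract gives 1,016 as the number to be recruited, and the Recruitment section aims to invite and enrol every eligible subject. The Sample size calculation requires 300.
- The Primary outcome section names T2DM incidence alongside adoption of healthy behaviours.
- The Data analysis plan compares T2DM incidence by Kaplan-Meier curves, log-rank tests and Cox regression with 95% confidence intervals.

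**The concern.** The power of a log-rank or Cox comparison depends on the number of events. With risks of 10% and 7%, about one participant in twelve would develop diabetes within 2 years, so 256 participants would supply roughly 22 events. That is far too few to detect a hazard ratio near 0.70 with 80% power. The paragraph gives no event count and no step from events to participants.

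T2DM incidence is a named primary outcome, and preventing or delaying T2DM is the primary objective. A reader who trusts the 80% figure would take a non-significant result as fair evidence that the messages do not reduce diabetes, when the trial had little chance of showing the planned effect.

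**Working it through.** **Inputs.** From the Sample size calculation: alpha 0.05 (sidedness not stated; two-sided assumed), power 80%, risks of 10% and 7% over 2 years, 300 participants, 20% loss. From the Data analysis plan: log-rank test. From the Abstract: 36 months and 1,016 people.

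**1. Reproducing 128 per group.** Two-sample exponential formula with no follow-up limit, h1 = 0.10, h2 = 0.07, mean 0.085:

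n per group = [1.96·√(2·0.085²) + 0.8416·√(0.10² + 0.07²)]² / 0.03² = (0.2356 + 0.1027)² / 0.0009 = 127.2, rounded up to 128, total 256.

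The match is exact. With no follow-up term, the formula in effect follows everyone until diabetes occurs. Event counts for a hazard ratio of 0.70 are close: Schoenfeld 4·(1.96 + 0.8416)²/(ln 0.70)² = 247; Freedman 253. One-sided versions give 195 to 202 and do not match.

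**2. Participants needed on the stated rates, before loss.**
- Two proportions, 10% versus 7%: 1,356 per group, 2,712 in total.
- Log-rank with 10% and 7% as cumulative risks: HR = ln 0.93/ln 0.90 = 0.689, needing 226 events. The mean 2-year risk is 8.5%, so 226/0.085 ≈ 2,660 participants. With HR 0.70, 247/0.085 ≈ 2,906.

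**3. Power on the stated rates.** Power = Φ(√d·|ln HR|/2 − 1.96), with d expected events and HR 0.689. At the same hazards, the 3-year risks are 1 − 0.90^1.5 = 14.6% and 1 − 0.93^1.5 = 10.3%, mean 12.5%.

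| Participants | Follow-up | Events | Power |
|---|---|---|---|
| 300 | 2 years | 25.5 | 15% |
| 300 | 3 years | 37.4 | 21% |
| 240 (completers only) | 2 years | 20.4 | 13% |
| 240 (completers only) | 3 years | 29.9 | 17% |
| 1,016 | 2 years | 86.4 | 41% |
| 1,016 | 3 years | 126.7 | 55% |

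A two-proportion check at 300 gives 15% at 2 years and 20% at 3 years.

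If people who drop out contribute follow-up until they leave, the loss is milder. Take exponential dropout reaching 20% at the end of follow-up, η = −ln(0.80)/T, with λ = −ln(0.90)/2 = 0.0527 and −ln(0.93)/2 = 0.0363 per year. The event probability is λ/(λ+η)·[1 − exp(−(λ+η)T)]. This gives 9.0% and 6.3% at 2 years (22.9 events, power 14%), and 13.1% and 9.3% at 3 years (33.6 events, power 19%).

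**4. Detectable effect.** With 37 events, 80% power needs HR = exp(−2·2.8016/√37) = 0.40.

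**5. Loss allowance.** 256/0.80 = 320, whereas 1 − 256/300 = 14.7%.

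**6. More generous readings.**
- Rates as annual hazards, 300 participants, no loss: 23% at 2 years (46.8 events), 31% at 3 years (67.3 events).
- One-sided test, 300 participants, 2 years: 23 to 24%.
- Annual hazards, all 1,016, 3 years: 77% with no loss (228 events), 67% with about 813 left after 20% loss.

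**The case against.** The best defence is that the document is not settled on 300. If all 1,016 are enrolled and the rates are read as annual hazards over 3 years with no loss, power reaches 77%. That reading conflicts with the words describing the rates, which tie them to 2 years. It also requires every person on the list to pass the inclusion and exclusion criteria, consent and stay, and it still falls short of 80%. What stands is that the conflict between 300 and 1,016 must be resolved before any power can be quoted.

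Several stronger readings are tempting, and the document does not support them:
- *256 was computed as an event count.* No formula or command is given. The origin is inferred from an exact match. What can be checked is that 256 is not the participant count for these inputs.
- *The 10% was taken from the earlier cohort and ignores background treatment.* The Study design section reports that "218 individuals had developed overt diabetes during the last 4 years", out of 1,234. Under a constant hazard and a full 4 years each, this is −ln(1 − 218/1,234)/4 = 0.0486 per year, or 9.3% over 2 years. The Lifestyle education section adds that "All participants will take Metformin 500 mg twice daily", and both arms receive group education. But no source is stated for the 10%, so closeness to 9.3% shows neither where it came from nor what it allows for. A request to justify the control rate is fair; a claim of error is not.
- *The 2-year horizon costs power in a 3-year trial.* It does not. At the same hazards, the third year adds about 12 events. It is a mismatch to reconcile.
- *The whole trial is underpowered.* Healthy-behaviour adoption is also a primary outcome, and nothing here bears on its power.

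**Conclusion.** The stated power is wrong for T2DM incidence. On the plan's own rates, two-sided 0.05 and constant hazards, 300 participants give about 15% power at 2 years and 21% at 3 years, or about 13 to 19% after 20% loss. Roughly 2,660 to 2,900 participants would be needed for 80% at 2 years before loss, about ten times 256.

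If the assumed effect is real, the comparison at 300 would be non-significant about 79 to 85% of the time, against the 20% implied. A reader might infer that a null result is close to certain. The figures do not go that far, and at 1,016 the chance of significance is about 41 to 55% before loss.

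The conclusion does not depend on how 256 arose, on the origin of the 10%, or on any assumed effect of background treatment. No reading examined reaches 80%. The loss allowance of 300 instead of 320 is a separate, smaller slip.

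**What to change.** Rewrite the Sample size calculation:
- Withdraw the statement that 256 (or 300) gives 80% power for T2DM incidence.
- Recompute by the log-rank method with administrative censoring at the actual 36-month follow-up and the stated 20% loss. State the sidedness of the test, and state the rates as cumulative risks or as hazards with their time unit.
- Reconcile 300 with the 1,016 in the Abstract. Give expected events, power and detectable hazard ratio (about 0.40 at 37 events) for the number really enrolled.
- Justify the control rate, or show results over a range.
- Say that a non-significant T2DM result will be interpreted through the hazard ratio and 95% confidence interval already planned, and not as evidence of no effect.

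The cost is one rewritten paragraph and one corrected recruitment figure. No extra participants are required. The downside is a much less favourable published power for a primary outcome.

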**Methods:**

This is a randomized controlled trial. One thousand and sixteen, eligible Saudi adults will be recruited from the Heart Health Promotion study (HHP), which was conducted at the King Saud University from July 2013 to April 2014. These adults were at a higher risk of developing T2DM within 2–3 years. The research team’s database has a contact list and they will recruit individuals over 6–8 weeks. All participants will be randomized at a 1:1 ratio into two groups, receive group education about lifestyle modifications and written information about diet and physical activity. Text 4 change SMS texts will be sent only to the intervention group. All participants will be assessed at baseline, 6, 12, 18, 24, 30, and 36 months for behavioral change using a World Health Organization (WHO) STEPS questionnaire and for glycated hemoglobin, biochemical and anthropometric measurements using standard methods.

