### Recruitment

Recruitment will take place over a 2-month period in order to ensure that all eligible subjects (from the HHP study) who fulfil the inclusion criteria are invited, give consent, and are enrolled following the steps of the baseline visits as shown in the flowchart (Fig. 1). The research team’s database has a contact list and they will recruit individuals over 6–8 weeks. Subsequently, they will be given a 6-month follow-up visit appointment.

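### The number to be enrolled is not reconciled (1016 or 300), and 300 is too few on its own inputs: its base of 256 behaves like an event count, so the stated 80% power is not there

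*Protocol article*

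**What the plan says.** Four places in the protocol article bear on the number enrolled.

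- Abstract, Methods: "One thousand and sixteen, eligible Saudi adults will be recruited from the Heart Health Promotion study (HHP").
- Study design: 1234 prediabetic subjects in the source study, less 218 who developed overt diabetes, and then "Therefore, 1016 are eligible for the present study".
- Recruitment: the two-month period is meant to ensure that "all eligible subjects (from the HHP study) who fulfil the inclusion criteria are invited, give consent, and are enrolled".
- Sample size calculation: "A sample size of 300 is required so that there are 150 participants each in the intervention and control groups".

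The last section takes diabetes hazard rates of 10% (control) and 7% (intervention) over two years, with "α = level of significance (0.05") and "β = Type II error (power of the study = 1- β = 80"%). From these it concludes that "the minimum sample size required to reject the null hypothesis is 256 (128 in each group"). The step to 300 is then: "With an expected loss of follow-up around 20%, the sample size was increased to 300 participants in total".

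**The concern.** Read together, these sections raise three problems.

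1. One reader will expect 1016 randomised, another 300. The document does not say whether 300 is a floor, a target or something else.
2. The 1016 is called eligible, but it results from a single subtraction. The trial's other criteria have not been applied: literacy, smartphone access, no contraindication to activity, exercise, diet regimen, myocardial infarction, renal function and pregnancy.
3. The increase from 256 to 300 looks too small for 20% loss. The 256 itself looks far too small for a comparison of 10% with 7%.

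The third problem has the most at stake. Incidence of type 2 diabetes is part of the primary outcome, and it is the only outcome for which a sample size is given. If the 80% does not follow from the inputs, a null result could be taken as evidence against the messages when the trial had little chance of detecting the planned effect.

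**Working it through.** **Inputs from the protocol article.** Source cohort 1234 and 218 converted (Study design); three-year trial (Study design); 1:1 allocation (abstract); rates 10% and 7% over two years, alpha 0.05, power 80%, minimum 256, loss about 20%, total 300 (Sample size calculation).

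**Assumptions.** Alpha is two-sided (the section does not say, but the two-sided form reproduces 256 and the one-sided form does not). Event times are exponential. Loss is exponential and reaches 20% at three years.

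**1. Where 1016 comes from.** 1234 − 218 = 1016. Only conversion to diabetes has been removed, so 1016 is an upper limit on enrolment.

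**2. Reproducing 256.** Take hazards 0.10 and 0.07, with mean 0.085, in the exponential hazard-difference formula without censoring:

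N = 2 × [z(0.975) × √(2 × 0.085²) + z(0.80) × √(0.10² + 0.07²)]² / (0.10 − 0.07)²

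- First term: 1.960 × 0.12021 = 0.2356
- Second term: 0.8416 × 0.12207 = 0.1027
- N = 2 × 0.3383² / 0.0009 = 254.4, so 128 per arm and 256 in total

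This matches the plan exactly. The one-sided form gives 200.6. No follow-up time enters the formula: it holds only if every participant is observed until diabetes develops. The required number of events at a hazard ratio of 0.70 is close to it: 247 (Schoenfeld) or 253 (Freedman). If follow-up is limited, with the variance term λ²/(1 − exp(−λT)), the same formula gives 1613 participants at T = 2 years and 1121 at T = 3, before any loss.

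**3. The allowance for loss, taking 256 at face value.**

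- 256 / 0.80 = 320
- Laxer multiplier: 256 × 1.20 = 307 (308 with equal arms)
- 300 × 0.80 = 240, which is 16 below 256
- 1 − 256/300 = 14.7%, the loss that 300 can absorb

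**4. Power for diabetes incidence.** The loss hazard is η = −ln(0.80)/3 = 0.0744. The chance of an observed event per person is λ/(λ + η) × [1 − exp(−3(λ + η))]. Expected events D equal N times the mean of this over the arms. Power is Φ(½ × √D × |ln HR| − 1.960).

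*Two-year risks:* λ = −ln(0.90)/2 = 0.0527 and −ln(0.93)/2 = 0.0363; HR = 0.689; event chances 0.131 and 0.093, mean 0.112.

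*Annual hazards:* λ = 0.10 and 0.07; HR = 0.70; event chances 0.234 and 0.170, mean 0.202.

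| N | Events, two-year risks | Power | Events, annual hazards | Power |
|---|---|---|---|---|
| 300 | 33.6 | 19% | 60.6 | 28% |
| 320 | 35.9 | 20% | 64.6 | 30% |
| 1016 (upper bound) | 113.8 | 51% | 205.3 | 72% |

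Example, first cell: ½ × √33.6 × 0.3728 − 1.960 = −0.88, and Φ(−0.88) = 0.19.

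For 80% power the Schoenfeld formula needs 226 events on the first reading and 247 on the second. None of the three sizes reaches that.

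**The case against.** The strongest defence is that 1016 is the sampling frame and 300 the minimum within it. Much of this stands. No section caps enrolment at 300, the calculation speaks of a minimum, and the Recruitment section enrols everyone who qualifies. A reader might infer that staff would not know whether to stop at 300. The document does not support that, because it contains no stopping rule at 300. What remains is the abstract's statement that 1016 will be recruited, the Study design's statement that 1016 are eligible, and the lack of any sentence relating either to 300.

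A reader might also infer that enrolling all would more than triple the events and give 51% power. Those figures hold only if all 1016 pass the remaining criteria and consent. They are ceilings.

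On the loss allowance, the stated loss is only approximate, and in a time-to-event analysis people lost still contribute time until censoring. So 240 understates the information kept. Still, 300 falls short under either inflation convention, and 14.7% is not close to 20%. The slip is small: moving to 320 adds about one or two points of power.

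Finally, the document does not show the formula behind 256. The no-censoring explanation rests on an exact numerical match and is not stated by the authors. The low power in the table does not depend on it.

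**Conclusion.** The point holds, in three parts of unequal weight.

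- **Enrolment wording.** The abstract, Study design, Recruitment and Sample size sections do not agree, and nothing reconciles them. This should be fixed and is a matter of wording.
- **Loss allowance.** On the plan's own inputs 300 should be 320 (or 307 by the laxer rule). This is a minor error.
- **Power.** This is the part that matters. The stated 80% is not delivered by 300, nor by 320. It is not reached even at the upper bound of 1016, on either reading of the rates.

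The power figures rest on two-sided alpha, exponential event times, three years of follow-up and 20% loss spread over that time. The text does not settle whether 10% and 7% are two-year risks or annual hazards, so both are shown. Correcting 300 to 320 might look like a complete repair, but it would keep a base of 256 that follows only if every participant develops diabetes under observation.

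**What to change.** 1. State one rule in the abstract, Study design, Recruitment and Sample size calculation: up to 1016 prediabetic subjects from the source study are invited, and every eligible, consenting person is randomised. Describe any required number as a minimum and not a cap.
2. In the abstract, say that the 1016 will be invited, not recruited. In the Study design, call them potentially eligible.
3. Redo the sample size from expected events. Say whether 10% and 7% are two-year risks or annual hazards, give the sidedness of alpha and the follow-up time, and divide by one minus the loss. Do not simply write 320 for 300.
4. Restate the power for diabetes incidence at a realistic enrolled number, and label any figure at 1016 as an upper bound.

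If the existing plan to enrol all who qualify stands, the cost is wording and one recalculation. Message volume, visits and laboratory work scale with the number actually randomised. The changes are best made before recruitment closes, since a cohort is hard to enlarge afterwards.
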